## Abstract

**Background:**

Around one third to one half of patients with hip fractures require red-cell pack transfusion. The increasing incidence of hip fracture has also raised the need for this scarce resource. Additionally, red-cell pack transfusions are not without complications which may involve excessive morbidity and mortality. This makes it necessary to develop blood-saving strategies. Our objective was to assess safety, efficacy, and cost-effictveness of combined treatment of i.v. ferric carboxymaltose and erythropoietin (EPOFE arm) versus i.v. ferric carboxymaltose (FE arm) versus a placebo (PLACEBO arm) in reducing the percentage of patients who receive blood transfusions, as well as mortality in the perioperative period of hip fracture intervention.

**Methods/Design:**

Multicentric, phase III, randomized, controlled, double blinded, parallel groups clinical trial. Patients > 65 years admitted to hospital with a hip fracture will be eligible to participate. Patients will be treated with either a single dosage of i.v. ferric carboxymaltose of 1 g and subcutaneous erythropoietin (40.000 IU), or i.v. ferric carboxymaltose and subcutaneous placebo, or i.v. placebo and subcutaneous placebo. Follow-up will be performed until 60 days after discharge, assessing transfusion needs, morbidity, mortality, safety, costs, and health-related quality of life. Intention to treat, as well as per protocol, and incremental cost-effectiveness analysis will be performed. The number of recruited patients per arm is set at 102, a total of 306 patients.

**Discussion:**

We think that this trial will contribute to the knowledge about the safety and efficacy of ferric carboxymaltose with/without erythropoietin in preventing red-cell pack transfusions in patients with hip fracture. ClinicalTrials.gov identifier: NCT01154491.

## Background

Hip fracture (HF) is highly prevalent in Spain, mainly affecting the elderly. It is estimated that 0.7% of women 65 years or older will suffer a hip fracture during their lifetime, and demographic trends predict that the demand for care will double in the next 40 years [1-3]. A total of 4-8% of these patients will die during hospitalization, and fewer than 25% will regain mobility and preserve autonomy at hospital discharge [4,5]. Socioeconomic burden associated to HF is enormous (40.000 euros (57.000 US dollars)) per patient [6].

Anemia is the one of the most frequent complications of HF; around one third to one half of patients will require red-cell pack(s) (RCP) transfusion [7]. RCP transfusion has been the classical choice in treating severe anemia of these patients [7]. Nevertheless, as already stated, the increasing incidence of HF in this population has also raised the need for this valuable and scarce resource. Additionally, RCP transfusions are not without complications [8-11]. In very old and often fragile patients, these effects may involve excess morbidity and mortality, making it necessary to develop blood-saving strategies (BSS) [9,12].

The most important factor in the development of anemia is blood loss, but some other mechanisms (renal failure, inflammation, iatrogenic hemodilution) are also implicated, prompting the choice of different therapeutic approaches [9,13,14]. These rely in three cornerstones: firstly minimizing blood loss in the operating room, secondly rationalizing RCP transfusion protocols, and thirdly enhancing bone-marrow red blood cell production [13-16]. Although evidence that this last measure saves RCP is weak, an increasing number of works have demonstrated notable reductions in RPC transfusion, nosocomial infections, hospital stay, and even survival [14-16]. Nevertheless, some biases in the nature of said studies could partly explain some of the obtained results.

All these previous studies were performed using 300 to 600 mg of intravenous iron sucrose administered in a period ranging from 2 to 6 days. Ferric carboxymaltose (FC) has considerable advantages over iron sucrose because it allows doses of 1 g in a single session, equivalent to 1000 mg of iron sucrose. Moreover, FC also provides an excellent tolerability and safety profile [17-19]. Therefore, it is very useful in situations where quick replacement is required as is the case of HF. It has been used successfully in iron deficiency-, inflammatory-, and in postpartum anemia, however there are no data on its efficacy in HF.

Preliminary results of perioperative use of EPO in HF are promising; however, these results suffer from bias because trials were not randomized and/or blinded. On the other hand, all studies were performed with iron sucrose, so that any additional benefit related to FC cannot be extrapolated. Therefore we have promoted and developed a phase III clinical trial (CT) in order to definitively assess the benefit of RCP saving with the use of EPO with/without FC in patients with HF. The main objective of the present CT was to evaluate the efficacy of combined treatment of i.v. ferric carboxymaltose and erythropoietin (EPOFE arm) versus i.v. ferric carboxymaltose (FE arm) versus placebo (placebo arm) in reducing the percentage of patients who receive blood transfusions in the perioperative period of hip fracture intervention.

## Methods

This is a multicentric, randomized, controlled, double blinded clinical trial of parallel groups, performed on adult in-hospital patients admitted with an HF. The eligible patients will be those admitted to the Emergency-Traumatology Services from the moment of admission until the moment of surgery. Inclusion and exclusion criteria are detailed in Table 1. Once the patient is eligible, meets inclusion criteria, does not meet any exclusion criteria and signs the informed consent form to participate in the clinical trial, the investigator will proceed to randomize the patient to the intervention group, and to perform the analytical extraction of blood count prior to the administration of the first dose of the trial drugs. The investigators will be responsible for having provided appropriate information about objectives, methods, anticipated benefits and potential risks to all eligible patients. If the patient is unable to read or to give consent, the legal representative must be present during the informed consent process and the legal representative will sign the consent form to attest that the information contained in the form has been explained and understood accurately and, where appropriate, to give consent. The investigator must also explain that patients are completely free to refuse to participate in the study or withdraw at any time for any reason.

**Table 1 T1:** Inclusion and exclusion criteria for entering the PAHFRAC-01 clinical trial

INCLUSION CRITERIA	EXCLUSION CRITERIA
Age ≥65 years	Bone marrow diseases which could interfere in the erythropoietic process (acute or chronic myelodysplastic syndromes or myeloproliferative diseases, and/or infiltration of the bone marrow due to solid or lymphatic neoplasm)

Osteoporotic hip fracture requiring surgical repair	Blood coagulation diseases or being currently treated with oral anticoagulants and/or heparin at therapeutic doses.

Hemoglobin levels between 90-120 g/L	Documented allergy and/or previous intolerance and/or contraindication of erythropoietin use and/or intravenous iron

Signed informed consent form	Patients with rheumatoid arthritis and/or another demonstrated origin of inflammatory anemia and/or not controlled arterial hypertension
	
	Patients with current or previous treatment for at least 3 months, with erythropoietin or intravenous iron
	
	Patients with chronic renal failure receiving hemodialysis or peritoneal dialysis

A randomization assignment list will be stratified by center. The randomization list for each center will be sent to the hospital Pharmacy Service at the time of the drug delivery. The person responsible for clinical trials in the Pharmacy Service will be the one responsible for keeping the blinded assignment. The allocation and blinding will be done by masking the syringes of EPO/placebo and iron infusion in the Pharmacy Service of each of the participating centers. The highest quality standards for handling parenteral medications will be kept for the preparation of intravenous mixtures. FC will be performed using plastic bags and opaque infusion sets.

Treatment will be administered in the three arms detailed in Table 2: Erythropoietin + Intravenous ferric carboxymaltose (EPOFE ARM); Placebo of Erythropoietin + Intravenous ferric carboxymaltose (FE ARM); Placebo of Erythropoietin + placebo of intravenous ferric carboxymaltose (PLACEBO ARM). The trial treatment will be administered, regardless of the arm, as soon as possible after inclusion, and always before surgery. Patients will receive the best standard treatment based on protocols existing in each hospital and the best medical care from both the internal medicine and orthopedic teams. Neither intravenous iron nor erythropoietin will be administered to the patient beyond that provided within the clinical trial. All patients could receive complementary oral iron if it is clinically indicated. Additionally, in clinical practice if the hemoglobin at discharge is less than 120 g/L, and no contraindications exits, oral iron regimen will be prescribed to the patient. The promotor's center (Hospital Universitario Virgen del Rocío) will provide the drugs for the trial, experimental and control treatments. The labeling and distribution of the study drugs will be managed by the Pharmacy Service of Virgen del Rocío University Hospital after having obtained the Spanish Regulatory approval for these procedures.

**Table 2 T2:** The three treatment arms of the PAHFRAC-01 clinical trial

TREATMENT ARM	TREATMENT DESCRIPTION
EPOFE ARM	Single dose of 40.000 IU of erythropoietin in a pre-filled 1 ml syringe, subcutaneously. Ferric carboxymaltose 1000 mg (two 500 mg vials diluted in a bottle of 250 ml of saline, in a plastic bag, and with an opaque infusion system), intravenously in a 20-min infusion.

FE ARM	Single dose placebo (saline) in a pre-filled 1 ml syringe, subcutaneously. Ferric carboxymaltose 1000 mg (two 500 mg vials diluted in a bottle of 250 ml of saline, in a plastic bag, and with an opaque infusion system), intravenously in a 20-min infusion.

PLACEBO ARM	Single dose placebo (saline) in a pre-filled 1 ml syringe, subcutaneously. Ferric carboxymaltose 1000 mg (two 500 mg vials diluted in a bottle of 250 ml of saline, in a plastic bag, and with an opaque infusion system), intravenously in a 20-min infusion.

Patients will be examined by the clinical support team and the Traumatology team at every visit during the study. The data will de classified by visit, and logged in the Clinical Report Data Form (Figure 1).

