### Statistical analysis

Both intention to treat (ITT) and per protocol analysis will be performed. The ITT analysis will include all patients who agreed to participate in the study, signed the informed consent, and had been randomized. Per protocol analysis will include the patients who were randomized, received the dose of erythropoietin and ferric carboxymaltose (EPOFE arm), ferric carboxymaltose (FE arm), or placebo (PLACEBO arm), and were operated on; excluding those who discontinued the trial, or received a red-cell pack in a different format than specified in the protocol. Violation of the blinded assignment will be also excluded in the per protocol analysis.

A chi-square test will be performed in order to establish the comparative analysis of the primary efficacy outcome, secondary efficacy, safety and cost endpoints between different arms of the study (Yates correction and, where necessary, Fisher exact test) for qualitative endpoints. Analysis of variance (with post-hoc test of Tukey and T3-Dunette)/Kruskal-Wallis test will be performed for quantitative variables. Differences between groups will be quantified using 95% confidence intervals.

The cost-effectiveness analysis will be performed by incremental cost-effectiveness method, using each patient who did not require RCP transfusion as the primary efficacy unit; each patient surviving at discharge and 60 days after discharge as the high efficiency unit; and the sum of all previously recorded costs of hospitalization as the cost unit. The calculations will be performed as follows: incremental cost-effectiveness (Euros per unit of efficiency gains) = NNT × (cost per a) option patient - cost per b) option patient).

All calculations will be performed using SPSS 18.0. The threshold of statistical significance is set at *p *< 0.05.

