### Interim analysis and stopping rules

An interim analysis will be performed when half of the patients are recruited, blinded to investigators in order to a) detect possible imbalances between the three arms of the trial with respect to a list of independent secondary endpoints, and b) assess whether the primary efficacy endpoint was obtained at this point in the trial. The list of independent secondary endpoints will include the following: age, sex, type of fracture (subcapital/intertrochanteric), baseline hemoglobin level and type of surgery.

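### The planned tests use neither the randomisation stratum (centre) nor baseline haemoglobin; they are valid but give up some precision that costs almost nothing to recover

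*Protocol article*

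**What the plan says.** On design, the Methods section of the protocol article states that "A randomization assignment list will be stratified by center". It lets background care vary by site: "Patients will receive the best standard treatment based on protocols existing in each hospital". It also has the investigator arrange, once a patient is eligible, "to perform the analytical extraction of blood count prior to the administration of the first dose of the trial drugs". Table 1 restricts entry to haemoglobin of 90 to 120 g/L.

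On analysis, the Statistical analysis section fixes the test for the primary outcome: "A chi-square test will be performed in order to establish the comparative analysis of the primary efficacy outcome". The same sentence extends it to the other categorical outcomes, with "Yates correction and, where necessary, Fisher exact test) for qualitative endpoints". For continuous outcomes it says: "Analysis of variance (with post-hoc test of Tukey and T3-Dunette)/Kruskal-Wallis test will be performed for quantitative variables". Under Outcome measures, these include mean haemoglobin at 24 hours, 72 hours and discharge.

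Baseline haemoglobin has one statistical use. The section on interim analysis and stopping rules lists it, ending with "baseline hemoglobin level and type of surgery", among the variables to be compared between arms at half recruitment. It does not say what follows if an imbalance is found. No stratified or covariate-adjusted analysis appears anywhere in the article.

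**The concern.** When allocation is stratified on a factor, the design removes between-stratum differences from the treatment contrast. An analysis that ignores the factor still counts those differences in its standard error, so the interval is wider than the design warrants. That is plausible for centre here, because care follows local protocols and transfusion practice may differ.

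Baseline haemoglobin is a natural candidate predictor of transfusion and of post-operative haemoglobin. Leaving it out keeps chance imbalance between arms as avoidable noise. If the interim check shows an imbalance, the only response left is an unplanned adjusted analysis, which carries less weight than a prespecified one.

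What is at stake is precision, not the validity of the trial's answer.

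**Working it through.** **The plan's own sample size.** Inputs from Sample size calculation: 60% v 40%, one-sided 0.05, 80% power.
- n = [1.645·√(2·0.5·0.5) + 0.842·√(0.24 + 0.24)]² / 0.20² = (1.163 + 0.583)² / 0.04 = 76.2, so 77 per arm.
- Continuity-corrected: (76.2/4)·[1 + √(1 + 4/(76.2·0.20))]² = 85.9, so 86 against the stated 87. The figure reproduces.
- Two-sided values would be 97 uncorrected and 107 corrected.
- Dropout: 87/0.85 = 102.35, stated as 102.

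Formula power of an uncorrected test is 84.5% one-sided and 75.6% two-sided at 87 per arm, and 89.2% and 82.0% at 102 per arm.

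**Effect of adjustment on the primary outcome.** The documents do not give the inputs, so these are assumed:
- 8 centres of 22 patients (88 per arm, EPOFE v placebo only), with exact balance within centre;
- haemoglobin uniform over 90 to 120 g/L;
- centre SD on the log-odds scale of 0 to 0.8;
- odds ratio for transfusion per 10 g/L higher haemoglobin of 1 to 0.4.

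Marginal rates were held at 60% and 40%. The adjusted analyses are linear risk-difference models with a t reference. There were 5000 simulated trials per scenario, so the standard error is about 0.6 points on each power. Two-sided power at 0.05, in %:

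| Centre SD, OR | Chi-square | Yates | Centre | Centre + Hb | Gain of centre + Hb over chi-square |
|---|---|---|---|---|---|
| 0, 1 | 77.9 | 73.8 | 76.4 | 76.5 | -1.4 |
| 0, 0.6 | 77.3 | 73.0 | 75.8 | 78.2 | +0.9 |
| 0.4, 0.6 | 78.6 | 73.9 | 78.8 | 79.9 | +1.3 |
| 0.4, 0.4 | 77.6 | 73.5 | 77.7 | 82.2 | +4.6 |
| 0.8, 0.6 | 78.7 | 74.5 | 80.7 | 82.5 | +3.8 |
| 0.8, 0.4 | 78.9 | 74.3 | 80.3 | 84.5 | +5.6 |

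- Centre alone changes power by -1.5 to +2.0 points over chi-square.
- Against the Yates test, centre plus haemoglobin gains 2.7 to 10.2 points, but 4.1 to 4.7 points separate plain chi-square from Yates in every row. That part comes from the continuity correction, not from adjustment.
- The standard error of the risk difference goes from about 0.073 unadjusted to 0.066–0.072 when haemoglobin is prognostic, and to 0.074 when neither factor is.

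**Size under the null.** At centre SD 0.8, chi-square rejects 4.1–4.4% and Yates 2.9–3.2%. With no centre or haemoglobin effect, Yates already rejects only 4.1%, so part of its conservatism is the correction itself. The linear model with centre and haemoglobin rejects 4.7–5.4% across all scenarios. A logistic Wald test with one term per centre rejected 5.2–6.2% with 8 centres.

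**Haemoglobin outcomes.** ANCOVA multiplies residual variance by 1 − r², where r is the correlation with baseline (assumed).
- r = 0.3: factor 0.91, so 87 per arm carries the information of 87/0.91 ≈ 96.
- r = 0.5: factor 0.75, equivalent to 116.
- r = 0.7: factor 0.51, equivalent to about 171.

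**The case against.** The strongest reply is that nothing here is an error. An unadjusted test after centre-stratified randomisation is valid, the article contradicts nothing, and covariate lists and pooling rules commonly sit in an analysis plan that is not shown. The first two parts stand. The last stands for the pooling rule, but the article does name the primary test and the tests for haemoglobin, and those tests leave out the stratification factor.

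It is also fair that the gain is uncertain and may be small. The entry range of 90 to 120 g/L limits how much haemoglobin can predict and would tend to lower r. Centre adjustment alone can cost power. A logistic Wald analysis also overstates the benefit. With 10 centres and 87 per arm (1500 trials per scenario), it raised power from 77.2% to 80.3% under moderate prognosis and from 79.5% to 86.0% under strong prognosis, but rejected 5.3% and 6.4% under the null. Rescaled to 5% by normal approximation, the gains of 3.1 and 6.5 points shrink to about 2.4 and 4.0.

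Two stronger readings are tempting, and the documents do not support them.
- A reader might infer that the trial is already short of its stated 80% power and needs adjustment to rescue it. The stated one-sided sample size reproduces, and the intention-to-treat set is all randomised patients, where 102 per arm gives 82.0% even two-sided. A shortfall appears only for a two-sided test at 87 per arm (75.6%), and sidedness is a separate question.
- A reader might infer that chance imbalance in baseline haemoglobin biases the result. Under randomisation the unadjusted test and interval already allow for such imbalance. It adds noise, not systematic error.

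**Conclusion.** The point holds as a loss of efficiency. The plan stratifies on centre and measures haemoglobin before dosing, then fixes analyses that use neither. For transfusion, the plausible change is about -1 to +6 points of two-sided power over a plain chi-square, mostly from haemoglobin. For the haemoglobin endpoints, which are secondary, the 9% to 49% cut in residual variance is the clearer benefit.

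That the tests ignore both factors is plain from the text. The sizes are not: they depend on assumed centre numbers, centre variation and prognostic strength, and they cover only EPOFE v placebo. The change is worth making because the possible loss is about 1 point of power, but the trial's validity does not depend on it.

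**What to change.** Amend the Statistical analysis section before unblinding.

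- **Primary outcome:** make the primary analysis one adjusted for centre and continuous baseline haemoglobin, reported as a standardised risk difference with 95% CI. Use a test that holds its size in small samples, such as a linear risk-difference model or a score or likelihood-based test, rather than a logistic Wald test with many centre terms. If a logistic model is used, its odds ratio is conditional, so the risk difference must be obtained by standardisation.
- **Simple check:** keep a centre-stratified Mantel-Haenszel test alongside it.
- **Haemoglobin at 24 hours, 72 hours and discharge:** use ANCOVA with baseline haemoglobin and centre in place of ANOVA or Kruskal-Wallis.
- **Small centres:** fix the pooling rule in advance, without reference to outcome by arm.

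The covariates are already collected, so the change is to wording only. The costs are the pooling rule, a slightly more complex analysis, and about 1 point of power if neither covariate turns out to be prognostic.

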**Figure 1 F1:**
[figure not shown]
**Scheme of the clinical trial visits in the three arms**. V0 = Visit 0; S = Surgery; V1 = Visit 1 (24 hours after surgery); V2 = Visit 2 (72 hours after surgery); V3 = Visit 3 (the day of hospital discharge); V4 = Visit 4 (60 days after hospital discharge). A = Ferric carboximaltose + Erythropoietin; B = Ferric carboximaltose + Placebo; C = Placebo + Placebo

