### Sample size calculation

Sample size was calculated as follows:

-To obtain statistical significance in the comparison between the i.v. iron + EPO arm compared to placebo. The treatment arm exclusively with iron is only used in the evaluation of results, but not in the sample size calculation.

-To obtain a confidence level of 95% and 80% power.

-To be single sided.

-To obtain a reduction in the primary endpoint of 20% (percentage of patients who need transfusions), which is considered as clinically significant in the literature. According to this, we would expect the percentage of patients who need to be transfused in the placebo group to be 60% and in the treatment group 40%.

-Sample size was calculated online using SISA http://www.quantitativeskills.com/sisa/calculations/samsize.htm. A total of 87 patients per arm are needed with the foregoing conditions.

-Taking into account a percentage of drop-outs of 15% per arm, the total number of patients per arm is set at 87 × (1/1-0.15) = 102, a total of 306 patients.

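### Table 2 gives the placebo arm the same treatment as the iron arm, including ferric carboxymaltose 1000 mg i.v.

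*Protocol article*

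**What the plan says.** The Methods text names the three arms and sends the reader to the table for their content: "Treatment will be administered in the three arms detailed in Table 2". The same sentence then defines the control arm as "Placebo of Erythropoietin + placebo of intravenous ferric carboxymaltose (PLACEBO ARM". The Abstract (Methods/Design) agrees, giving the third treatment as "or i.v. placebo and subcutaneous placebo". The Figure 1 legend lists the iron arm and the control arm as different treatments: "B = Ferric carboximaltose + Placebo; C = Placebo + Placebo".

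Table 2 says something else. Its iron-only row begins "FE ARM Single dose placebo (saline) in a pre-filled 1 ml syringe, subcutaneously. Ferric carboxymaltose 1000 mg", and its control row begins "PLACEBO ARM Single dose placebo (saline) in a pre-filled 1 ml syringe, subcutaneously. Ferric carboxymaltose 1000 mg". Both rows then continue in the same words to the end of the cell.

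Two further statements bear on the point. The Methods exclude iron from any other intravenous source: "Neither intravenous iron nor erythropoietin will be administered to the patient beyond that provided within the clinical trial". The Sample size calculation section bases the trial size on a single contrast: "To obtain statistical significance in the comparison between the i.v. iron + EPO arm compared to placebo".

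**The concern.** The table and the text cannot both be right about what control patients receive. Table 2 is the only place in this document that describes the infusions at preparation level (vials, diluent volume, bag, line, duration), and in the control row that description is of the active drug.

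What is at stake is the identity of the comparator. Intravenous iron and erythropoietin outside the trial are barred, so the trial infusion alone determines whether a control patient is free of intravenous iron. If the row were followed:

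- FE and PLACEBO would be one treatment under two labels, and the comparison of iron with placebo in the main objective (end of Background) would disappear.
- EPOFE versus PLACEBO, the contrast on which the trial was sized, would estimate the effect of erythropoietin given on top of iron. The assumed transfusion rates of 60% and 40% were set for a placebo control and would no longer describe that contrast.
- The fault would be hard to see on the ward, because the infusions are masked in the pharmacy and run through opaque sets.

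**Working it through.** **1. The plan's own figures.** The Sample size calculation section gives 60% versus 40% transfused, 95% confidence, one-sided, 80% power, 87 per arm, then 15% drop-out.

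- Without continuity correction: n = [1.645 × √(2 × 0.5 × 0.5) + 0.842 × √(0.6 × 0.4 + 0.4 × 0.6)]² / 0.20² = (1.163 + 0.583)² / 0.04 ≈ 76.2, so 77.
- With continuity correction: n = (76.2 / 4) × [1 + √(1 + 4 / (76.2 × 0.20))]² ≈ 85.9, so 86, within one patient of the stated 87.
- Drop-out: 87 / (1 − 0.15) = 102.35, stated as 102. Total: 3 × 102 = 306.

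The stated size is therefore that of a comparison with placebo. Nothing in it depends on the wording of Table 2.

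**2. The two rows compared.** The descriptions after the arm label were compared as strings. They are identical: 11 words for the subcutaneous part plus 32 for the intravenous part, 43 in all. The 32-word intravenous part is also the same in the EPOFE row, so all three rows specify active iron.

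**3. The sources side by side.**

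| Source | Control arm, s.c. | Control arm, i.v. |
|---|---|---|
| Abstract, Methods/Design | placebo | placebo |
| Methods, text on the arms | placebo | placebo |
| Figure 1 legend, arm C | placebo | placebo |
| Table 2, PLACEBO row | placebo (saline) | ferric carboxymaltose 1000 mg |

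**4. What each reading implies for the planned patients.**

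- Table 2 as printed: iron in 3 of 3 arms, 3 × 102 = 306 of 306 patients; two distinct treatments.
- The other three sources: iron in 2 of 3 arms, 2 × 102 = 204 of 306 patients; three distinct treatments.
- Difference: 306 − 204 = 102, the planned control arm.

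**5. Could it be a reading artefact?** The row is complete and grammatical, carries its own label, and gives dose, vials, diluent, line and duration. It does not look like a broken or truncated table. No amendment log or superseded text is involved.

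**6. Which version is intended?** Three consistent statements, and the row's own label, stand against the row's content. A row copied from the one above and left unedited explains this best. That cause is an inference; the contradiction itself is not.

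**The case against.** The strongest reply is that the document resolves the slip itself. The sentence that points to Table 2 goes straight on to define the control arm correctly. The Background also names placebo as a separate comparator, and the per-protocol definition in the Statistical analysis section distinguishes patients who received iron from those who received placebo. No careful reader would doubt the intention. The consequences are all conditional, since nothing says that infusions were prepared from this table: drug supply, labelling and masking run through the pharmacies, whose documents are not shown. The patient counts only multiply one row by the arm size. And a condensed article may properly leave the placebo's vehicle and volume to the full protocol.

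Most of this is fair. A copy error is the likely cause, no mis-dosing is shown, and the counts measure neither bias nor lost power. The absence of a vehicle and volume for the placebo is not a fault in itself; the question arises only because a corrected row must describe the infusion.

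None of it makes the row right. The article has not omitted a detail here. It states a specific wrong treatment for one arm of a placebo-controlled drug trial, in the table it names as the source for arm content. That the right answer can be recovered from elsewhere is a reason to expect a simple correction, not a reason to leave the row standing.

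**Conclusion.** The concern holds, with high confidence. As printed, Table 2 assigns ferric carboxymaltose 1000 mg i.v. to the control arm and so contradicts three other statements in the same document. Its extent is one table row, covering the treatment of 102 of the 306 planned patients on paper.

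The contradiction rests on the printed text alone and needs no assumption. Two further readings are inferences: that the row is a copying mistake, and that placebo by both routes was always intended. No claim is made about how the trial was conducted, about bias, or about power. The correction is required because the row misidentifies the comparator.

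**What to change.** Replace the intravenous part of the PLACEBO row so that it describes an iron-free infusion matched to the active one, for example: *placebo for ferric carboxymaltose, bagged and run through an opaque line as in the other two arms, given i.v. over 20 minutes*. The subcutaneous part stays as it is.

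The sponsor should confirm the vehicle and volume before the row is finalised. By analogy with the other rows it is presumably 250 ml of saline without iron, but the document does not say so for the placebo.

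As a precaution, check the pharmacy preparation documents against the corrected row and, for anyone already treated, the dispensing records.

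The cost is one corrected row, one confirmation and one document check. No extra patients are needed, and the sample size and analysis stay as planned.
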